#### **4.5 Co-enrolment Criteria**

As indicated in Section 4.4, participants should not take part in other research studies involving drugs, devices, vaccines, or other clinical research while taking part in this study. Each site will be responsible for defining procedures for management and prevention of co-enrolment prior to site initiation. Participation in studies not involving biomedical interventions will be permitted.

Exceptions to this co-enrolment prohibition may be made for the following types of studies, at the discretion of the site investigator /designee:

- Ancillary studies developed and approved by the ECHO management team
- Interventional studies for persons with HIV infection for those women who seroconvert during the trial

---

 This will not be known until enrolment, when in a woman who is randomized to IUD, difficulty is noted passing a uterine sound

 May be enrolled after treatment

Should any participant report or should study staff discover concurrent participation in contraindicated studies after randomisation, the site investigator/designee will consult the ECHO operations team regarding on-going product use and other potential safety considerations associated with co-enrolment.

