#### 4.4.2 Exclusion Criteria

A woman who reports or is found to have any of the following criteria will be excluded from the study:

- Medical contraindications (Category 3 or 4 criteria as detailed in the WHO MEC to DMPA, LNG implant, or copper IUDs, including
  - Persistent measured blood pressure 160/100 mmHg or higher, or history of uncontrolled hypertension due to vascular disease
  - History of a stroke or heart attack
  - History of rheumatic disease such as lupus, with positive or unknown antiphospholipid antibodies or low platelet count
  - Multiple risk factors for cardiovascular disease including two or more of: a) smoked regularly for the past 6 months, b) history of hypertension, c) history of diabetes, and d) history of abnormal cholesterol/lipid disorder
  - Diabetes for more than 20 years or diabetes with nephropathy, retinopathy, or neuropathy
  - A current/acute blood clot in her legs or lungs
  - History of severe liver cirrhosis or a liver tumor
  - Current or previous breast cancer
  - Endometrial, ovarian, or cervical cancer

---

 World Health Organization (WHO), *Medical eligibility criteria for contraceptive use*. 5th ed 2015, Geneva: WHO

- History of trophoblastic disease
- Unexplained vaginal bleeding between menstrual periods or bleeding after intercourse
- History of pelvic tuberculosis
- Anatomical abnormality of the uterus incompatible with IUD insertion
- A recent septic abortion
- Untreated mucopurulent cervicitis on exam, untreated pelvic inflammatory disease (PID), or untreated known gonorrhoea or chlamydia
- Has received a DMPA or NET-En injection in the last 6 months
- Has used an implant or an IUD in the last 6 months
- Is pregnant or intending to become pregnant in the next 18 months
- Has had a hysterectomy or sterilization
- Has previously enrolled in the study
- Has any condition (social or medical), which in the opinion of the investigator, would make study participation unsafe or complicate data interpretation.

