### **5.4.2 Physical exam**

Trained clinicians will do brief physical exams on all potential participants at screening to evaluate for contraindications to the study methods. These exams will include measurement of blood pressure, height, and weight, and pelvic exams. At the time of the pelvic exam an endocervical swab will be taken to test for *Neisseria gonorrhoeae* and *Chlamydia trachomatis*. A bimanual exam will be performed to assess for the presence of any uterine or cervical anomalies that would preclude IUD use (see Section 4.4.2). Any suspected reproductive tract infections identified on physical exam will be treated syndromically, according to local standards of care. In addition, treatment will be initiated and/or adjusted as appropriate based on lab results when available.

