## 5.6 Enrolment visit

Sites will schedule women for enrolment visits within a minimum of 1 day to a maximum of 6 weeks (42 days) of screening. To ensure that women requesting contraception are not delayed sites will attempt to have most women return within 1 week for enrolment. If a potential participant returns for enrolment beyond 42 days, she may be rescreened and then enrolled on the same day. At enrolment, sites will review study eligibility, and obtain enrolment informed consent or parental consent and assent from minor participants for women under the age of legal consent (for sites which opt to use separate screening and enrolment consents only). Study staff will collect limited medical, reproductive, and behavioural data. Women will provide urine for pregnancy testing and blood for plasma archiving. Sites will randomise eligible women (at which point a woman will be considered enrolled) and women will receive one of the three study contraceptive methods. Women will also be scheduled for their 1-month contraceptive follow-up visit (Table 3 & Appendix 6).

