| Clinical   |       | 
 
Obtain/update medical, contraceptive, reproductive history/data
 
Administer assigned contraceptive method (which will include a pelvic exam for women randomized to IUD)
 
Conduct syndromic assessment/treatment for STIs/RTIs
 
 |
| Laboratory | Urine | 
 
Test urine for pregnancy
 
                                                                                                                                                                                                           |
|                   | Blood | 
 
Collect blood for plasma/serum archive
 
Collect blood for HSV-2 testing
 
                                                                                                                                                                |

If a woman has had a clinician verified (by medical record review, knowledge of completed evacuation of uterus, observation of the expelled products of conception, or ultrasound confirmation) miscarriage or pregnancy termination within 12 days, a urine pregnancy test is not required. If such a woman has a pregnancy test done which is positive, she may still be enrolled.

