### **8.2.1 Primary analysis**

The primary study objective is to compare the risks of HIV acquisition among women randomised to DMPA, LNG implant, and the copper IUD. The primary analysis will include computation of the hazard ratios of HIV seroconversion based on a proportional hazards (PH) regression model, stratified on site. Only contraceptive method group will be included in the primary stratified model. An appropriate interim spending function will be used to account for interim analyses and control the type I error for each comparison at the 0.04 level. Women will be analysed according to their randomised contraceptive method, regardless of method switching; only women who are found to have been HIV-infected at enrolment (defined by a positive HIV RNA PCR test on the archived enrolment plasma sample) or who fail to contribute a follow-up HIV test result will be excluded from the primary analysis. Women who do not HIV seroconvert during the study will have their time in analysis censored at the date of their last negative HIV test result.

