### **Adverse events**

AEs that are either serious or result in method discontinuation will be summarised in frequency tables (including both the number of each type of AE and the number of distinct participants ever reporting each type of AE), by system organ class and preferred MedDRA term.

The study will compare rates of SAEs between contraceptive groups using two-sided 95% confidence intervals based on exact Poisson methods. Results will be reported overall, by relatedness, and by geographical region. The analysis will be conducted both according to randomised contraceptive method group and restricted to periods with exposure to each contraceptive method.

The study will similarly compare rates of AEs resulting in method discontinuation between groups using two-sided 95% confidence intervals. This analysis will exclude women who never adopted their assigned method, and will be based on time to first method discontinuation.

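### Section 4.4.2 with footnote 2 can be read as a post-randomisation exclusion in the IUD arm only, and no passage says that the woman stays in follow-up

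*Protocol*

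**What the plan says.** The lead-in to the exclusion list in Protocol 4.4.2 reads "A woman who reports or is found to have any of the following criteria will be excluded from the study". One listed item is "Anatomical abnormality of the uterus incompatible with IUD insertion". Footnote 2, attached to that item and printed at the end of 4.5, adds "This will not be known until enrolment, when in a woman who is randomized to IUD, difficulty is noted passing a uterine sound".

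Section 5.6 fixes the moment of enrolment: "Sites will randomise eligible women (at which point a woman will be considered enrolled"; the method is given after that. Table 3 describes administration of the assigned method at the enrolment visit as a step "which will include a pelvic exam for women randomized to IUD". Appendix 6 likewise marks the enrolment pelvic examination as IUD only.

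Section 5.4.2 places a check earlier and in everyone, at screening: "A bimanual exam will be performed to assess for the presence of any uterine or cervical anomalies that would preclude IUD use". It refers back to 4.4.2.

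For the primary analysis, 8.2.1 states "Women will be analysed according to their randomised contraceptive method, regardless of method switching". It allows only two exclusions: HIV infection already present at enrolment, and no follow-up HIV test result.

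**The concern.** Taken together, the lead-in to 4.4.2, footnote 2 and 5.6 describe a woman who is randomised, therefore enrolled, and then found to meet an exclusion criterion by a procedure that only the IUD arm undergoes. Women with the same anatomy in the other two arms are not sounded, so they stay in.

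Section 9.4.3 tells sites to follow the protocol without deviation. A site could reasonably conclude that the woman must come off study. The 1-month visit carries no HIV test (Appendix 6), and the first scheduled follow-up test is at month 3 (5.7.2). A woman taken out at enrolment would therefore either have no follow-up test and meet the second permitted exclusion in 8.2.1, or contribute almost no time at risk.

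What is at stake is a one-sided selection that touches both comparisons involving the IUD, in a trial justified in 2.2 by its protection against selection bias. Sites may also read the passages differently from one another. An analysis plan cannot repair this afterwards, because HIV tests that were never taken cannot be recovered.

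**Working it through.** **Step 1. The passages side by side.**

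- *When the abnormality is found.* Footnote 2 says not until enrolment, on sounding. Section 5.4.2 says at screening, by bimanual examination in all women. Both can be true only if each covers part of the cases: those palpable at screening (all arms, before randomisation) and those detected only by sounding (IUD arm, after randomisation).
- *What happens to her.* The lead-in to 4.4.2 says excluded from the study. Section 5.4.10 says that stopping or changing the method is no reason to leave the study, but it does not mention a woman found to meet an exclusion criterion. Section 4.6.5 asks women who discontinue a method to keep attending, but she never started one. Section 5.15 commits the team to retaining women once enrolled. No passage says expressly that she stays in follow-up.
- *How she is analysed.* Section 8.2.1 keeps her in the IUD arm if she has a follow-up HIV test. If she leaves at enrolment without one, the same section removes her.

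**Step 2. The plan's own figures.** Section 8.1 gives 250 events per pairwise comparison for a hazard ratio (HR) of 1.5, 80% power, two-sided alpha 0.04 and up to 10% dilution. By Schoenfeld's formula, events = 4 × (2.054 + 0.842)² / (ln HR)².

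- 10% off the excess risk, HR 1.45: 243 events.
- 10% off ln HR, HR 1.44: 252 events.

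The stated 250 reproduces. The smallest significant HR at 250 events is exp(2.054 / √(250/4)) = 1.297, which matches the value of about 1.3 in 8.2.5.

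**Step 3. Size if the women are removed.** Neither of these inputs is in the documents; both are assumptions:

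- f, the fraction of the IUD arm removed: 1-2%. With 2,600 women per arm, 2,600 × 0.01 = 26 and 2,600 × 0.02 = 52.
- r, the HIV risk of removed women relative to those kept: 0.5 to 2.

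The comparator arm keeps its women with the same anatomy. With no true difference, the observed HR (DMPA or implant versus IUD) is therefore (1 − f) + f × r. Starting from 125 events per arm, the IUD arm keeps 125 × (1 − f) / [(1 − f) + f × r] events. Type I error uses SE = √(1/125 + 1/IUD events) and the critical value 2.054.

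| f | women removed | r | null HR | events | type I error |
|---|---|---|---|---|---|
| 1% | 26 | 0.5 | 0.995 | 249.4 | 0.0402 |
| 1% | 26 | 1 | 1.000 | 248.8 | 0.0400 |
| 1% | 26 | 2 | 1.010 | 247.5 | 0.0406 |
| 2% | 52 | 0.5 | 0.990 | 248.7 | 0.0406 |
| 2% | 52 | 1 | 1.000 | 247.5 | 0.0400 |
| 2% | 52 | 2 | 1.020 | 245.1 | 0.0424 |

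Worked line for f = 2%, r = 2: HR = 0.98 + 0.04 = 1.02; IUD events = 125 × 0.98 / 1.02 = 120.1; total = 245.1. At HR 1.44, power goes from 0.797 with 250 events to 0.789 with 245.1.

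As a stress case, f = 5% (130 women) gives a null HR of 0.975 to 1.05 and a type I error of up to 0.054. Nothing in the documents suggests a fraction that high.

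The DMPA versus implant comparison is not affected.

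**The case against.** The best defence is that footnote 2 says only when the abnormality becomes known, not that the woman leaves the study, and that almost every rule for enrolled women points towards keeping her. Randomisation is enrolment (5.6). The team makes every reasonable effort to retain enrolled women (5.15). Not using the assigned method is no ground for leaving (5.4.10). The per-protocol analysis in 8.2.4 censors women who never start their method, so the plan expects non-starters to be present in the primary analysis. A woman who does leave has a final visit with an HIV test (5.7.3, Table 5), so having no follow-up test is not a certain outcome.

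Most of this stands. It makes the harm conditional on how a site reads 4.4.2. It does not remove the conflict: the lead-in says excluded, no passage exempts her, and a final-visit test on or near the enrolment day would add almost no person-time.

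Three stronger readings are tempting, and the documents do not support them.

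- A reader might infer that the criterion can be met only after randomisation and only in the IUD arm. The screening bimanual examination in 5.4.2 contradicts this; it is true only of cases found on sounding.
- A reader might infer that the as-randomised comparison is broken. Section 8.2.1 excludes no one for failed insertion or late-found ineligibility, so a woman kept in follow-up stays in her arm.
- A reader might infer that insertion-related adverse events vanish from the IUD arm, because 8.2.2 says of the adverse-event discontinuation analysis "This analysis will exclude women who never adopted their assigned method". That rule applies to all arms and does not depend on footnote 2, and a method never started cannot be discontinued. Events are monitored from randomisation (9.2.4), and serious ones are compared by randomised group (8.2.2).

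**Conclusion.** The point holds as a wording conflict with a possible, small consequence. Read literally, 4.4.2 with footnote 2 and 5.6 yields an exclusion after randomisation in one arm, which does not fit the as-randomised rule in 8.2.1 or the retention provisions in 4.6.5, 5.4.10 and 5.15.

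If sites acted on that reading, the null HR for each IUD comparison would move by at most about 2%, against a significance threshold of about 1.3. Type I error would be at most about 0.042. This rests on an assumed 1-2% removed and a risk ratio between 0.5 and 2. The direction is unknown, and at equal risk there is no bias, only a small loss of events. The 250-event design figure is not in question. Severity is minor; the reason to act is that the problem is avoidable and cannot be corrected once follow-up has been lost.

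**What to change.** Reconcile footnote 2 with 4.4.2, 5.4.2, 5.6 and 8.2.1, so that the protocol says one thing about when this abnormality is assessed and what follows when it is found late. How the eligibility criterion itself is worded is a clinical matter for the protocol team.

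Add one sentence: a woman in whom this finding is made after randomisation remains enrolled, is HIV-tested on the full schedule and is analysed in her randomised arm. This says nothing about her contraceptive care.

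The cost is a short clarification and a few women followed off their assigned method. The resulting dilution is slight, and 8.1 already allows up to 10% for person-time off the allocated method. The sample size, event target and alpha do not change.

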#### **4.6 Interventions**

Study procedures including provision of contraceptives will begin only after the study has been approved by participating IRBs and applicable regulatory authorities for each of the participating sites.

##### **4.6.1 Description/ Regimen of Study products**

Sites will randomise each enrolled participant to one of three study interventions: DMPA, LNG implant or the copper T380-A IUD. Product manufacturing, labelling, and management information will be documented in a Clinical Supplies Management Plan.

##### **4.6.2 Administration/insertion of study products**

###### *DMPA administration*

For women randomised to DMPA, site staff will inject the initial IM injection of DMPA (medroxyprogesterone acetate sterile aqueous suspension 150 mg per 1 mL) at enrolment. Subsequent injections will be given every 3 months (i.e., at quarterly study visits) at the study site.

Sites will assess participants who are more than 4 weeks late for their DMPA injections for pregnancy prior to administering a subsequent injection.

###### *LNG implant insertion*

Women randomised to implants will receive LNG implants at enrolment. Trained clinicians will insert the implants under the skin of a woman's inner side of the upper arm using standard manufacturer recommended techniques. Sites will observe women for 10 minutes after implant insertion. Women will be shown how to palpate for the rods.

###### *T380a Copper IUD insertion*

Women randomised to IUDs will receive their IUDs at enrolment. Trained providers will insert T380a copper IUDs using standard insertion techniques. During the screening visit, all participants will be screened for gonorrhoea and chlamydia. Participants do not need to have available gonorrhoea and chlamydia testing results to receive their IUDs, and scheduling of the enrolment visit should not be delayed to wait for results. If test results return before enrolment and are positive the participant should be called back and treated appropriately, and the IUD may be inserted immediately. If a participant has clinical signs or symptoms of PID, or mucopurulent cervical discharge at time of the enrolment visit, treatment will be provided and IUD insertion will be delayed by at least 7 days. For a few asymptomatic women, IUD insertion might occur before a positive screening test result becomes available. In these participants, treatment will commence as soon as possible once results of a positive test are received. IUDs do not need to be removed. This will not impact participant safety; treatment of PID after IUD insertion, as well as same-day insertion protocols have been shown to be effective and safe [61-63].

##### **4.6.3 Supply and accountability**

Study sites will start administering contraceptive products only after the study has been approved by participating IRBs and applicable regulatory authorities. Each study site will order contraceptives on a timely basis to ensure a sufficient supply throughout the study.

Sites will store study contraceptives according to the labelled storage requirements for each product in a limited access securely locked area. For purposes of inventory accountability, the study site will make supplies of hormonal

contraceptives obtained for the study available only to study staff and these contraceptives will be provided only to women enrolled in the study.

#### **4.6.4 Strategies for successful contraceptive initiation and assessing continuation**

##### *Ensuring successful insertion of IUDs and implants*

Physician education and training regarding the few contraindications to, and the low risks of, inserting IUDs in young and nulliparous women will be conducted prior to study initiation with refresher trainings as needed. In addition, sites will screen all women for chlamydia and gonorrhoea and treat those with positive results.

Experienced trainers will train site clinical personnel in standardised IUD and implant insertion before the study begins. Only providers trained and skilled in insertion and removal of implants and IUDs will do insertions and/or removals during the study.

##### *Assessing method continuation*

The study team will assess contraceptive method use by study records and participant self-report. Sites will request that women receive their DMPA injections at the study sites, and administered injections will be recorded directly. If a participant reports getting an injection elsewhere, she will be asked to show her contraceptive record (if available); otherwise she will be asked to recall to the best of her ability the date of her last injection. Sites will ask women using implants or IUDs about continued use at each regular visit. For women in the implant arm, implant presence will be verified by palpation at each visit. At the final study visit, study clinicians will validate presence of the implant by palpation of the implant site and presence of the IUD by visualization of IUD strings. Inability to verify the presence of either the IUD or the implant will lead to radiologic tests for confirmation.

##### *Improving method continuation*

In general, continuation rates for contraceptive methods, particularly progestin-only injectables, are lower in typical-use settings than is desired for this trial. Before randomisation, trained study staff will counsel women extensively on the importance of using their assigned methods for their full study participation. The local communities will be engaged to defray contraceptive myths and misperceptions and potential obstacles to method initiation or continuation in the target population. Strategies for promoting method continuation and retention will be developed that engage study site leaders, study site staff, current contraceptive users, and the family planning clinic community. All participants will return at one month to assess any early problems with their methods. Trained staff will repeat structured counselling at each scheduled study follow-up visit to maximise method continuation. Furthermore, study staff will ask any study participant who is considering discontinuing her method to come discuss this before doing so, so that the study staff can help with any issues about method side effects and to dispel any myths. By advising women ahead of time about potential side effects of the method and how to manage them, as well as having a contraceptive "trouble-shooting" visit one month after enrolment and ensuring availability of study staff for contraceptive counselling at any time the study team anticipates that method continuation will be higher than what has been reported in standard practice (Section 2.6).

